## Abstract

**Background:** Imeglimin is a novel type 2 diabetes (T2D) drug that is expected to improve mitochondrial function. In its phase 3 clinical trials in Japanese patients with T2D, the hemoglobin A1c (HbA1c) decrease following imeglimin administration was slow, reaching a plateau after 20–24 weeks of treatment. In general, the erythrocyte lifespan may be a factor when HbA1c shows an abnormal value. Therefore, this study will comparatively evaluate HbA1c and other markers of glycemic control in patients with T2D after imeglimin administration and also examine the effects of imeglimin on erythrocytes.

**Methods:** This single-arm, open-label, prospective, exploratory study is designed to evaluate the divergence between HbA1c and glycoalbumin (GA) or 1,5-anhydroglucitol (1,5-AG) and the glycemic reduction rate in 30 patients with T2D with inadequate glycemic control when imeglimin 2,000 mg is administered for 6 months. In addition, we will examine the effect on erythrocytes, the presumed cause of this divergence. We will measure sustained glycemic variability using flash glucose monitoring and examine the relationship between changes in these indices and HbA1c. Moreover, because prolonged erythrocyte lifespan is a possible cause of falsely high HbA1c levels, erythrocyte lifespan, erythrocyte deformability, and hemoglobin concentration will be evaluated as effects of imeglimin on erythrocytes. Furthermore, if imeglimin has an ameliorative effect on erythrocyte deformability, it may improve peripheral arterial disease; thus, we will also evaluate the toe-brachial pressure index, a measure of this effect.

**Discussion:** In this study, if imeglimin administration results in diverging rates of hypoglycemic effect between HbA1c and GA or 1,5-AG and prolongs erythrocyte lifespan, GA and 1,5-AG, rather than HbA1c, will be considered appropriate measures of the hypoglycemic effect in the early stages of imeglimin administration. If imeglimin improves erythrocyte deformability, it may also be a new treatment strategy for peripheral arterial disease, a chronic complication of T2D.

**Ethics and dissemination:** The study protocol was scientifically and ethically reviewed and approved by the Certified Clinical Research Review Board of Toho University (approval number: THU22002). The study protocol was registered in the Japan Registry of Clinical Trials (jRCT) in December 2022 (jRCTs031220489).

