## 2 Methods/design

### 2.1 Design

The INFINITY study (Comparative evaluation of clinical glycemic control markers treated with ImeglimiN and its eFfect on erythrocytes IN patIents with TYpe 2 diabetes mellitus) is a single-center, single-arm, open-label, prospective study. In clinical practice, the hypoglycemic effect of imeglimin in patients with T2D may differ when measured by HbA1c and GA levels. This study will be conducted in a single-arm, exploratory study (Table 1) because the prolonging of erythrocyte lifespan is postulated as the cause of this divergence. This study will compare HbA1c with the rate of glycemic reduction over time for GA or 1.5-AG to assess whether HbA1c is an appropriate measure. Continuous blood glucose variability measured using flash glucose monitoring (FGM) will also be examined related to changes in these indices to ensure reliability. In addition, because the effect of imeglimin on erythrocyte lifespan is a possible cause of HbA1c deviation, hemoglobin concentration, erythrocyte lifespan, and erythrocyte deformability will also be examined as effects on erythrocytes. Furthermore, if imeglimin ameliorates erythrocyte deformability, it is expected to have the potential to improve peripheral arterial occlusive disease, so an index of arteriosclerosis will also be measured.

**TABLE 1 T1:** Overview of visits and tests schedule.

Item	At informed consent	Pre-observation (months)		Observation period (months)							Follow-up period (months)			At discontinuation		
		−2	−1	0	1	2	3	4	5	6	7	8	9	
Allowable ranges of visits (±weeks)		±2	±2	±2	±2	±2	±2	±2	±2	±2	±2	±2	±2			
Informed consent	X															
Demography	X															
Study drug adherence					X	X	X	X	X	X				X		
Height, body weight				X	X	X	X	X	X	X	X	X	X	X		
Blood pressure, pulse rate				X	X	X	X	X	X	X	X	X	X	X		
Blood tests		X	X	X	X	X	X	X	X	X	X	X	X	X		
Urinalysis				X	X	X	X	X	X	X	X	X	X	X		
Erythrocyte lifespan		X	X	X	X	X	X	X	X	X	X	X	X	X		
Erythrocyte deformability			X	X	X	X	X	X	X	X	X	X	X	X		
Arteriosclerosis/inflammation test				X						X			X	X		
FGM test		X	X	X	X	X	X									
Adverse events		X	X	X	X	X	X	X	X	X	X	X	X	X		

Abbreviations: FGM, flash glucose monitoring.

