#### 2.3.2 Secondary outcomes

Items 1–4 below will be compared between baseline (month 0) and each time point in the pre-observation, observation, and follow-up periods, and between 6 months after imeglimin administration and each time point in the follow-up period. The change from baseline (maximum and mean values) in the pre-observation and observation periods will also be evaluated.1. Erythrocyte lifespan

Erythrocyte lifespan is calculated by measuring the carbon monoxide (CO) concentration in exhaled breath using a Carbolizer (Taiyo Co., Ltd., Osaka, Japan) and using the Strocchi et al., formula shown below (Strocchi et al., 1992):

Erythrocyte lifespan (days) = K × hemoglobin (g/mL)/endogenous CO (ppm).

K = 1380 (conversion factor).2. Erythrocyte deformability

Erythrocyte deformability is measured using a blood fluidity measuring device MC-FAN (Optima Inc., Tokyo, Japan). The microchannel array passage time of 100 μL heparinized whole blood is an index for blood fluidity.3. Red blood cell count, white blood cell count, hemoglobin concentration, and hematocrit (Ht)4. Corpuscular constant (mean corpuscular volume: MCV, mean corpuscular hemoglobin concentration: MCHC, mean corpuscular hemoglobin content: MCH)

Items 5 and 6 below will be compared between baseline and the pre-observation or observation periods.5. Measured values of HbA1c, GA, and 1,5-AG, change from baseline, and percent reduction in blood glucose with baseline as 100% (percent reduction in blood glucose will also be compared between each index at each time point)6. GA/HbA1c and 1,5-AG/HbA1c ratios

For items 7 and 8 below, data measured by the FGM system using FreeStyle Libre Pro (Abbott Diabetes Care Inc., Alameda, CA, United States of America) will be used to compare baseline with each time point during the observation period (up to 3 months after imeglimin administration). FreeStyle Libre Pro should be used following the package insert.7. Change in mean daily glucose levels and percentage decrease in blood glucose (baseline is the day before imeglimin administration)8. Mean 14-day glucose levels, estimated HbA1c levels, glucose management indicator (GMI), and respective percentage decreases in glycemia (baseline is 14 days before imeglimin administration):

Estimated HbA1c (%) = (mean glucose [mmol/L] + 2.59)/1.59.

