GMI (%) = 3.31 + 0.02392 × (mean glucose [mg/dL])9. Comparison of measured HbA1c levels and estimated HbA1c values at each time point in the pre- and post-observation periods and the respective percentage reduction in blood glucose at each time point

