## 3 Discussion

In this study, the effect of imeglimin administration on lowering blood glucose in type 2 diabetic patients with inadequate glycemic control will be measured using HbA1c, GA and 1,5-AG as indices. The divergence between HbA1c and the rate of blood glucose-lowering with GA and 1,5-AG will be evaluated whether HbA1c is an appropriate index for imeglimin administration. The effect of imeglimin on erythrocytes will also be examined as a cause of the divergence. If imeglimin lengthens erythrocyte lifespan, HbA1c is not an appropriate measure of the hypoglycemic effect of imeglimin in the early stages of administration, but GA and 1,5-AG are appropriate measures to evaluate instead. If imeglimin improves erythrocyte deformability, imeglimin may be a new treatment strategy for peripheral arterial occlusive disease, a chronic complication of T2D.

In the TIMES 1–3 studies, imeglimin, both as monotherapy and in combination with other antidiabetic drugs, slowly decreases HbA1c, reaching a plateau around 24 weeks after administration (Dubourg et al., 2021; Dubourg et al., 2022; Reilhac et al., 2022). Furthermore, the fasting blood glucose trend in the TIMES 1 (monotherapy) study (106 subjects) showed a large decline at week 4 and plateaued from weeks 8 to 24 (Pharmaceuticals and Medical Devices Agency, 2021). This observation differed from the slowly declining trend of HbA1c, which was measured simultaneously. We also reported in a retrospective observational study that, under routine medical care, imeglimin treatment of type 2 diabetic patients resulted in a slower decrease in HbA1c than GA, with a divergence in the rate of change between the two (Osonoi et al., 2022a; Osonoi et al., 2022b). These results suggest that HbA1c may appear to be high. To assess whether HbA1c is an appropriate measure, this study will ensure reliability by comparing HbA1c with the rate of decrease in blood glucose over time for GA or 1.5-AG and by measuring sustained blood glucose variability with FGM and its association with changes in these measures.

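### The stated conclusion endorses GA and 1,5-AG on conditions that can only discredit HbA1c; no listed outcome sets either marker against sensor glucose

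*Protocol article*

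**What the plan says.** The conclusion appears twice, with different conditions. In the Discussion, longer erythrocyte survival is the only condition, and the conclusion drawn from it is: "HbA1c is not an appropriate measure of the hypoglycemic effect of imeglimin in the early stages of administration, but GA and 1,5-AG are appropriate measures". In the Abstract, divergence between HbA1c and GA or 1,5-AG is required as well: if imeglimin produces divergence and "prolongs erythrocyte lifespan, GA and 1,5-AG, rather than HbA1c, will be considered appropriate measures of the hypoglycemic effect in the early stages".

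Section 2.1 (Design), directly after naming HbA1c, GA and 1,5-AG, promises a check against the sensor: "Continuous blood glucose variability measured using flash glucose monitoring (FGM) will also be examined related to changes in these indices to ensure reliability". The Discussion repeats the promise. The Abstract speaks of relating the sensor indices to HbA1c only.

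Section 2.3.2 then lists the outcomes. Outcome 5 compares the three blood markers with baseline and with one another ("percent reduction in blood glucose will also be compared between each index at each time point"). Outcome 6 is "GA/HbA1c and 1,5-AG/HbA1c ratios". Outcomes 7 and 8 compare sensor measures with their own baseline, up to month 3. Outcome 9 is the one place where a blood marker meets the sensor: "Comparison of measured HbA1c levels and estimated HbA1c values at each time point in the pre- and post-observation periods".

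**The concern.** Longer erythrocyte lifespan is a reason to think HbA1c reads high. It says nothing about GA or 1,5-AG. Divergence shows that markers disagree, not which of them follows glucose. The step from HbA1c being misleading to GA and 1,5-AG being right needs evidence on GA and 1,5-AG themselves, and in this single-arm trial the only independent glucose reference is FGM.

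At stake is the trial's main practical message, that early response to imeglimin should be judged by GA and 1,5-AG. Suppose lifespan is prolonged and imeglimin also moves GA or 1,5-AG for reasons unrelated to glucose. The rule would then reject HbA1c with some reason and put an unverified marker in its place, and no result it calls for would reveal the problem.

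**Working it through.** The plan gives no figure on this point. The check is a reading of the outcome list, followed by two pieces of arithmetic.

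**1. What each listed outcome compares (section 2.3.2)**

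| Outcome | Comparison | HbA1c vs sensor | GA or 1,5-AG vs sensor |
|---|---|---|---|
| 5 | Blood markers vs baseline and vs each other | no | no |
| 6 | GA and 1,5-AG as ratios to HbA1c | no | no |
| 7, 8 | Sensor measures vs their own baseline | no | no |
| 9 | Measured vs sensor-estimated HbA1c | yes | no |

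Outcomes 1–4 concern erythrocytes and blood counts. The safety and exploratory outcomes contain no marker-versus-sensor comparison.

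**2. Does the conclusion respond to how GA behaves?** Suppose lifespan is prolonged and HbA1c and GA diverge.

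| True state on drug | Conclusion under the Abstract | Conclusion under the Discussion |
|---|---|---|
| GA follows glucose | GA appropriate | GA appropriate |
| GA shifts for other reasons | GA appropriate | GA appropriate |

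The answer is the same in both rows. The same holds for 1,5-AG.

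**3. Could the percentage reductions in outcomes 5, 7 and 8 stand in for a direct comparison?** Take the protocol's own formulas and assume, for illustration, that mean glucose falls from 180 to 150 mg/dL (10.0 to 8.33 mmol/L).

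- Mean glucose: (180 − 150)/180 = 16.7% fall.
- Estimated HbA1c: (10.0 + 2.59)/1.59 = 7.92; (8.33 + 2.59)/1.59 = 6.87; fall 1.05/7.92 = 13.2%.
- GMI: 3.31 + 0.02392 × 180 = 7.62; 3.31 + 0.02392 × 150 = 6.90; fall 0.72/7.62 = 9.4%.

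These are three exact functions of one glucose value, yet their percentage falls are 16.7, 13.2 and 9.4. Unequal percentage reductions between indices therefore cannot show that one of them misreads glucose.

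**4. What data are available?** In Table 1, FGM is marked at months −2, −1, 0, 1, 2 and 3, and blood tests are marked at all of these.

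- Scheduled maximum: 30 × 6 = 180 pairs per marker, nominally 30 × 3 = 90 up to baseline and 90 on drug.
- If only the 24 patients required by section 2.6 contribute: 24 × 6 = 144.
- Table 1 does not say whether a sensor period comes before or after its visit, and imeglimin starts within 1 week of the baseline examination. If no month-0 sensor period could be used as pre-drug, the maximum is 30 × 5 = 150, of which 60 are pre-drug.

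The Introduction says GA reflects glucose changes over 2–3 weeks (14–21 days), close to the 14-day sensor mean in outcome 8. The protocol states no window for 1,5-AG.

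**The case against.** A reader might infer that the plan endorses GA and 1,5-AG merely because HbA1c diverges from them. It does not. Both statements of the rule require longer lifespan, and the Discussion explains that this makes HbA1c falsely high. The lifespan condition is a real reason to place the error in HbA1c.

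Nor does a shift in GA or 1,5-AG unrelated to glucose trigger the rule by itself. It would not lengthen erythrocyte lifespan, and outcome 9 would then show measured HbA1c agreeing with the sensor estimate. That guards against wrongly blaming HbA1c. It does not guard against endorsing GA or 1,5-AG when HbA1c is rightly blamed.

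It would also be too strong to say that the two markers will never be tested against glucose, or that the sensor data go unused. Section 2.1 and the Discussion announce an association between FGM and the indices, outcomes 7–9 use the sensor data, and the unseen analysis plan may supply a method. I accept this. But the published conclusion is not conditional on any such result, and a method added in the analysis plan would not change that. The Discussion also frames the FGM work as a test of whether HbA1c is appropriate, not GA or 1,5-AG.

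Finally, the study is exploratory, admits that it is small and single-arm, and has hemoglobin as its primary outcome. That limits the weight of the point but does not remove it.

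**Conclusion.** The point holds in this form. The rule in the Abstract and Discussion would endorse GA and 1,5-AG on evidence that does not test them. The comparison that would test them is announced in prose, absent from the nine listed secondary outcomes, and not required by the conclusion. The documents do not support the stronger claims that divergence alone triggers the conclusion or that no check is intended.

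The effect is on interpretation. The primary outcome and its sample size are untouched, but the main practical recommendation would rest on an unsupported step. No numerical bias can be given, because the documents contain nothing on how GA or 1,5-AG relates to sensor glucose on imeglimin. The 180 pairs are a scheduled ceiling, not an expected yield, and pairs within a patient are not independent.

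**What to change.** - **Outcome.** Extend secondary outcome 9 to GA and 1,5-AG, using the FGM and blood tests already scheduled at months −2 to 3. Keep sensor days on drug out of the pre-drug period, in line with outcome 8, whose baseline is the 14 days before administration.
- **Model.** For each marker, fit a within-patient (mixed) model on 14-day mean sensor glucose with a pre-drug/on-drug term. That term estimates how far the marker moves at the same sensor glucose.
- **Reporting.** Give the shift with its 95% confidence interval. Do not read a non-significant term as no change: with about 24 to 30 patients, an imprecise result would pass that test. The analysis plan should state before database lock how large a shift still counts as tracking glucose; the documents offer no basis for a value, so none is suggested here.
- **Conclusion.** In the Abstract and Discussion, call GA or 1,5-AG appropriate only where its own result supports it, marker by marker, and give the same conditions in both places. Otherwise conclude only that HbA1c disagrees with the other markers and, if outcome 9 shows it, with sensor glucose.

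This needs no new visits, tests or patients. The cost is one added analysis, a reworded conclusion, and a claim that is harder to reach.

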**FIGURE 1 F1:**
[figure not shown]
Potential cellular and mitochondrial mechanisms of the action of imeglimin in erythrocytes, pancreas, skeletal muscle, and liver. NAMPT, nicotinamide phosphoribosyltransferase; NAD^+^, nicotinamide adenine dinucleotide; Ca^2+^, calcium ion; ATP, adenosine triphosphate; Complex I, mitochondrial respiratory chain complex I; ROS, reactive oxygen species.

Although this study is limited by being a small-scale, single-arm, open-label study, it is the first prospective interventional study to evaluate not only the divergence between HbA1c and GA or 1,5-AG on the hypoglycemic effect of imeglimin but also its effect on erythrocytes.

### 3.1 Trial status

The study protocol was fixed on 11 November 2022, and enrollment started on 14 February 2023. Enrollment is expected to be completed by 31 December 2023.

## 4 Ethics and dissemination

Before the study, the study protocol was scientifically and ethically reviewed and approved by the CRB of Toho University (approval number: THU22002). The study protocol was registered in the Japan Registry of Clinical Trials (jRCT) in December 2022 (jRCTs031220489). This study will be conducted at the Naka Kinen Clinic in accordance with the ethical principles of the Declaration of Helsinki and in compliance with the “Clinical Research Act.” The physician in charge of the study will provide sufficient explanation to the study participants using the consent and explanation documents and will obtain their free and voluntary consent in writing. The results of this study will be published through submission to a peer-reviewed scientific journal.

## Data Availability

The original contributions presented in the study are included in the article/supplementary material further inquiries can be directed to the corresponding author.
